### Sample size

2.7

This study is a small-scale, prospective, preliminary clinical study to verify the feasibility and treatment effects of a large-scale clinical trial. Therefore, an accurate sample size must not be determined. Based on a previous study suggesting a minimum of 12 subjects per group for a pilot study in biomedical science,^[28]^ the number of subjects to be recruited and the minimum range for efficacy evaluation is set as 16, considering a 20% dropout rate, a total of 40 subjects will be recruited.

### Recruitment

2.8

COPD patients receiving pharmacological treatment are recruited from the Division of Pulmonology of the Kyung Hee University Medical Center. This clinical trial is to be conducted at the Kyung Hee University Korean Medicine Hospital Clinical Trial Center. The purpose of this study is explained to the subjects, and screening is conducted among those who signed the informed consent form.

### Data management and monitoring

2.9

Data are managed by independent third parties. All documents related to the clinical study will be safely stored by the principal investigator or the person in charge or head of the testing agency and the clinical study manager for data security. The source document for this study will be stored in a separate locked space or in a computer database with limited access. Only the principal investigator and sub-investigators delegated by the principal investigator can access the data. Monitoring may be carried out via phone or a regular visit to the testing agency for the clinical study. The monitor upon visit should check the original copy of the basic data of the subjects, record of procedures, and data storage (clinical study files). The monitor should also oversee the progress of the clinical study and discuss it with the investigator if a problem arises.

### Ethics

2.10

This trial was approved by the IRB of the Kyung Hee University Korean Medicine Hospital (KOMCIRB 2020-12-006-002). The protocol complied with both the Declaration of Helsinki and the GCP Guidelines. Signed informed consent forms will be obtained from all eligible participants before enrollment.

This trial is registered with the Korean Clinical Trial Registry (KCT0006119).

### Statistical methods

2.11

Statistical significance is based on the significance level 0.05 with a power of 0.8.

Intended to treat, ITT: The subjects who underwent CMT at least once and performed the 6-MWT as the primary outcome.Per protocol, PP: The subjects who received the CMT intervention up to 80% or higher and performed the relevant tests.For all analyses, the ITT is the main analysis, while the PP is carried out simultaneously, and their results are presented together.

For continuous variables, the results are presented as mean and standard deviation, for which an independent *t* test or Mann–Whitney *U* test will be carried out. If the normality assumption is satisfied, an independent *t* test will be carried out; otherwise, the Mann–Whitney *U* test will be carried out. To adjust for the influence of age, ANCOVA with age as a covariate will be carried out. If a significant intergroup difference is found related to the baseline values, ANCOVA with age and baseline as covariates will be carried out. For missing values, the last measured value will be used for each subject based on the last observation carried forward (LOCF).

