## Abstract

**Background:**

In chronic obstructive pulmonary disease (COPD) management, greater emphasis has been placed on symptomatic improvement and enhanced quality of life in patients. Manual therapy among respiratory rehabilitation programs has received much attention recently, with the publication of numerous studies. In South Korea, a method known as Chuna Manual Therapy (CMT) has been applied in the management of COPD patients and in clinical practice, but the clinical basis for safety and effectiveness is yet to be established. Therefore, rigorously designed randomized controlled trials are required. We aimed to evaluate the feasibility of assessing the add-on effect and safety of CMT administered with standard Western medicine therapy for the treatment of COPD.

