**Methods:**

This is a randomized, single-blind, single-center clinical pilot trial. Patients with COPD receiving standard drug therapy are randomly divided into an experimental group (n = 20) and a control group (n = 20) at a 1:1 ratio. The experimental group receives CMT adding to the standard medical therapy once a week for 8 weeks. The control group receives only the standard drug treatment. The trial is conducted with an outcome assessor and statistician blinding. The primary outcome is the 6-minute walk test. The secondary outcomes include the pulmonary function test, the Modified Medical Research Council, visual analog scale for dyspnea, COPD assessment test, quality of life using the St. George's respiratory questionnaire, EuroQOL five dimensions questionnaire, and Korean pattern identification questionnaire. Adverse events are also be evaluated.

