### Objective and design

2.1

The primary purpose of this study is to verify the effectiveness and safety of CMT in combination with Western medicine therapy for COPD. The patients receiving COPD treatments are randomized into two groups: the experimental group for a combination of CMT and Western medicine therapy and the control group for Western medicine therapy only, while the intervention is performed for 8 weeks, once a week. The study will be conducted as a prospective, single-center, single-blinded, exploratory clinical study, and based on the results, the sample size for future large-scale clinical trials will be determined. The feasibility of the study protocol will also be evaluated. A flow diagram of this study is shown in Figure 1.

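### The stated power of 0.8 has no effect size or calculation behind it and contradicts the sample-size section of a self-declared pilot

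*Protocol article*

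**What the plan says.** Section 2.11 (Statistical methods) opens with: "Statistical significance is based on the significance level 0.05 with a power of 0.8". It does not say which difference the power refers to, or whether the test is one- or two-sided.

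Section 2.7 (Sample size) describes a small preliminary study and states: "Therefore, an accurate sample size must not be determined". Its basis for the number of patients is "a previous study suggesting a minimum of 12 subjects per group for a pilot study in biomedical science". It continues: "the minimum range for efficacy evaluation is set as 16, considering a 20% dropout rate, a total of 40 subjects will be recruited". The abstract gives the allocation as "randomly divided into an experimental group (n = 20) and a control group (n = 20) at a 1:1 ratio".

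The purpose is described in two ways. Section 2.1 (Objective and design) says: "The primary purpose of this study is to verify the effectiveness and safety of CMT in combination with Western medicine therapy for COPD". The abstract says: "We aimed to evaluate the feasibility of assessing the add-on effect and safety of CMT". Section 2.1 itself goes on to call the trial an "exploratory clinical study, and based on the results, the sample size for future large-scale clinical trials will be determined".

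**The concern.** Power is the probability of a significant result when a specified true difference exists. Without a difference and an SD, a power of 0.8 describes nothing. Here the figure also sits beside a section that disclaims any formal calculation. The sentence is loosely built as well, since statistical significance does not depend on power.

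Read together, Sections 2.1 and 2.11 suggest a trial designed to verify an effect with 80% power. The abstract and Section 2.7 describe a pilot with no power calculation. A reader who relies on the first pair could give a non-significant 6-MWT result, or a significant one, more weight than 40 patients can bear. Section 2.1 says that the results will set the size of a later trial, so the report should be clear about how precise they are.

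**Working it through.** **Inputs from the article.** Significance level 0.05 and power 0.8 (Section 2.11); 16 evaluable, 20% dropout and 40 in total (Section 2.7); 20 per arm (abstract); a continuous primary outcome, the 6-MWT (Section 2.5.1), compared by an independent t test, or by a Mann–Whitney test if normality fails (Section 2.11).

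**Inputs not given, and therefore assumed.** Sidedness (two-sided, with one-sided also shown); the true effect (a range in SD units); no covariate adjustment in the base case. The article gives no SD for the 6-MWT, so nothing can be converted to metres. Section 2.7 does not say that the 16 is per arm; that is inferred from step 1.

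**1. The plan's own figure.** 16 / (1 − 0.20) = 20 per arm, and 2 × 20 = 40. This matches Section 2.7 and the abstract.

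**2. The stated power.** It cannot be recomputed, because no difference or SD is given.

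**3. Difference detectable with 80% power.** By normal approximation, d = (1.960 + 0.842) × √(2/n):

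- n = 20: 2.802 × 0.316 = 0.89 SD
- n = 16: 2.802 × 0.354 = 0.99 SD

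With the noncentral t distribution, which suits these sizes better:

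| Test at level 0.05 | 20 per arm | 16 per arm |
|---|---|---|
| Two-sided t test | 0.91 SD | 1.02 SD |
| One-sided t test | 0.80 SD | 0.90 SD |
| Mann–Whitney, two-sided (relative efficiency 0.955) | 0.93 SD | 1.05 SD |

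**4. Power for assumed effects (two-sided t test, unadjusted).**

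| Assumed effect | 20 per arm | 16 per arm |
|---|---|---|
| 0.3 SD | 15% | 13% |
| 0.5 SD | 34% | 28% |
| 0.8 SD | 69% | 59% |

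For scale, 80% power at 0.5 SD would need 64 per arm.

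**5. Sensitivity to adjustment.** ANCOVA on baseline multiplies the detectable difference by √(1 − r²), where r is the correlation between baseline and follow-up. For an assumed r of 0.5 to 0.7:

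- 20 per arm: 0.909 × 0.866 = 0.79 SD, down to 0.909 × 0.714 = 0.65 SD
- 16 per arm: 1.024 × 0.866 = 0.89 SD, down to 1.024 × 0.714 = 0.73 SD

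Section 2.11 adds baseline as a covariate only if the groups differ significantly on it, so this gain cannot be counted on.

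**6. Precision.** The half-width of the unadjusted 95% confidence interval is t × √(2/n) in SD units: 2.024 × √(2/20) = 0.64 SD with 20 per arm, and 2.042 × √(2/16) = 0.72 SD with 16.

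**The case against.** The strongest reply is that a pilot needs no power calculation, and that the article says plainly that it is one. The abstract, the Introduction and Sections 2.1 and 2.7 all use pilot, exploratory, preliminary or feasibility language. Section 2.7 tells the reader that no formal size was derived, and Section 2.1 qualifies its own opening sentence within the same paragraph. No stated arithmetic fails. Much of this stands: the small sample is not the fault, the objective is loosely worded rather than plainly contrary, and an attentive reader has the means to discount the 0.8.

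It does not rescue the power phrase. The article makes a positive statement that its own sample-size section contradicts, so this is not a detail left to an unseen analysis plan. If the 0.8 was meant for the future trial, the text does not say so.

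A reader might go further and infer that the decision on the large trial is likely to be wrong. The article does not support that. It states no go/no-go rule and does not make the later trial depend on p < 0.05: Section 2.1 uses the results to set its size, and Section 3.1 simply expects it to follow the analysis. Nor can one say that a non-significant result is to be expected if the therapy works, because that depends on an assumed effect of about 0.5 SD that the article neither gives nor rules out.

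**Conclusion.** The stated power of 0.8 is unsupported and contradicts Section 2.7. The primary purpose in Section 2.1 claims more than this design can deliver and does not match the abstract.

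On a two-sided 0.05 unadjusted t test, the trial has 80% power only for differences of about 0.91 SD (20 per arm) to 1.02 SD (16 per arm), or about 0.80 to 0.90 SD if one-sided. If the true effect were 0.5 SD, power would be about 34% to 28%. These figures rest on the assumed sidedness, on no baseline adjustment, and on reading the 16 as per arm.

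This is a should-fix point of consistency. It is neither an arithmetic error nor a reason to enlarge the pilot.

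**What to change.** - **Section 2.11:** delete the reference to power, or label 0.8 explicitly as an assumption for the future trial.
- **Section 2.7 or 2.11:** state that the pilot is not powered for efficacy. Give the detectable difference with its assumptions: about 0.91 to 1.02 SD for 20 to 16 per arm, two-sided 0.05, unadjusted. State the sidedness of the test, and say that the 16 is per arm if that is what is meant.
- **Section 2.1:** state the primary purpose as feasibility and estimation of the effect and safety of the therapy, in line with the abstract and with that section's own exploratory description. The Discussion (Section 3) repeats the verification wording and should follow.
- **Conclusions:** base them on the 6-MWT difference with its 95% confidence interval, not on a claim that effectiveness has been verified.

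The cost is wording only. The stated figure becomes less favourable, and enrolment does not change. Section 3.1 reports recruitment as ongoing, so the correction is best made before the data are analysed.

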#### Inclusion criteria

2.3.1

1.Patients aged between 40 and 80 years2.Patients who satisfy the COPD clinical diagnostic criteria (forced expiratory volume in one second [FEV1] / forced vital capacity [FVC] < 0.70 on the Spirometry)^[1]^ and receiving the standard drug therapy3.Patients who voluntarily signs and submits the written consent for participation in the present clinical study

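### The main analysis set, labelled ITT, requires at least one CMT session and a performed 6-MWT: as written it admits no control patient, and on any reading it is not intention to treat

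*Protocol article*

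**What the plan says.** Section 2.11 of the protocol article (Statistical methods) defines two analysis sets. The main one is "Intended to treat, ITT: The subjects who underwent CMT at least once and performed the 6-MWT as the primary outcome". The other is "Per protocol, PP: The subjects who received the CMT intervention up to 80% or higher and performed the relevant tests". Their roles are fixed by "For all analyses, the ITT is the main analysis, while the PP is carried out simultaneously, and their results are presented together".

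The abstract (Methods) says of the comparator: "The control group receives only the standard drug treatment". Sections 2.1 and 2.2 agree that CMT is given in the experimental arm only. Patients are "randomly divided into an experimental group (n = 20) and a control group (n = 20) at a 1:1 ratio".

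Section 2.11 also plans an independent t test or Mann–Whitney U test and ANCOVA, and carries the last observation forward for missing values. No section says how a control patient enters either analysis set.

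**The concern.** An intention-to-treat set is fixed at randomisation. This one depends on two things that happen afterwards: receiving CMT and performing the 6-MWT. The first cannot happen to a control patient, so the rule conflicts with the design and with the two-group tests in the same section.

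Whoever runs the analysis will have to admit controls by a rule that the article does not state. A CMT patient who never attends would then be left out, while a control patient has no comparable way to be left out for not being treated. Patients are not blinded (section 2.2), so the decision not to start can depend on knowing the allocation. It may also be related to fitness or motivation, and so to walking distance.

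The set governs the primary 6-MWT comparison. Section 2.1 says the results will determine the sample size of later large trials, so an effect estimate and SD from a selected set would be carried forward under a label that misdescribes them.

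**Working it through.** **Inputs from the document**
- Allocation 20 and 20 (abstract, Methods).
- 16 evaluable per group and 20% dropout, 40 in total (section 2.7).
- 8 weekly sessions (abstract and section 2.1).
- Set definitions (section 2.11).
- Standard drug therapy as an entry criterion (section 2.3.1): "and receiving the standard drug therapy".

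**The plan's own figure.** 16 / (1 − 0.20) = 20 per group, and 2 × 20 = 40. The stated total is reproduced and is not affected by this point.

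**Literal reading.** A patient must have had CMT at least once and have performed the 6-MWT.
- CMT arm: at most 20 qualify.
- Control arm: 0 of 20 qualify.
- The per-protocol set also has 0 controls.

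**Softer reading.** Apply the CMT condition to the CMT arm only and the 6-MWT condition to both arms. Let k be the CMT patients never treated and m the further patients in each arm without a 6-MWT (both assumed). The set sizes are 20 − k − m for CMT and 20 − m for control.

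| k | m | CMT | Control |
|---|---|---|---|
| 0 | 4 | 16 | 16 |
| 2 | 0 | 18 | 20 |
| 2 | 2 | 16 | 18 |
| 4 | 4 | 12 | 16 |

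The imbalance comes from k alone; m can reduce both arms.

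**Third reading.** If the condition is taken as having received the allocated treatment at least once, it formally covers both arms. Controls meet it almost automatically, because being on standard drug therapy is required for entry. It still acts mainly on the CMT arm.

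**Illustration of the one-sided part.** Suppose a fraction f of the CMT arm never starts, and the tendency to start correlates ρ with 6-MWT distance (normal model, no true effect). The mean of those kept then exceeds the full-arm mean by ρ·φ(q)/(1 − f) SD, where q is the f-quantile of the standard normal distribution. Neither f nor ρ is in the document.
- f = 0.05 (1 of 20): φ(q)/(1 − f) = 0.103/0.95 = 0.109, so the shift is 0.03 SD (ρ = 0.3) to 0.05 SD (ρ = 0.5).
- f = 0.10 (2 of 20): 0.175/0.90 = 0.195, so the shift is 0.06 to 0.10 SD.

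A simpler cross-check assumes that non-starters would walk 0.5 to 1.0 SD less than the rest of the arm. The shift is then (k/20) × deficit: 0.025 to 0.05 SD for k = 1 and 0.05 to 0.10 SD for k = 2.

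For scale, the standard error of a difference with 20 per arm is √(2/20) = 0.32 SD.

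**Per-protocol threshold.** The wording in "The subjects who received the CMT intervention up to 80% or higher and performed the relevant tests" points both ways, as a ceiling and as a floor. If a floor is meant, 0.80 × 8 = 6.4 sessions, so at least 7 of 8 (87.5%).

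**The case against.** The strongest reply is that this is a drafting slip. Section 2.11 plans two-group tests, so a two-arm set is plainly intended, and nobody would analyse 20 against 0. That is fair as a forecast, and the realistic outcome is a mislabelled modified ITT set. It does not repair the definition: the article states a rule that is wrong, which is different from leaving detail to a fuller document, and no other section corrects it.

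Three stronger readings are tempting and are not supported.

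- A reader might infer that, once controls are admitted, only the CMT arm loses patients. The 6-MWT is measured in both arms, so that condition can exclude controls too. Only the CMT condition is one-sided.
- A reader might put the 20% from section 2.7 into the formula as the share of the CMT arm filtered out, which gives 0.105 to 0.175 SD. But that section reads "is set as 16, considering a 20% dropout rate, a total of 40 subjects will be recruited": it is planned dropout in both groups, not a never-treated rate in one. A CMT patient who leaves after one session still meets the CMT condition.
- A reader might infer that the bias must favour CMT. That is plausible if non-starters are less fit, but no data in the article show it, and the visit schedule in Table 1, which would show the control arm's visit burden, is not reproduced in the text at hand.

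It is also fair to say that a per-protocol set filters on adherence by design, and that a session threshold can apply only to the arm with sessions. What remains there is the missing rule for controls and the unclear threshold.

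**Conclusion.** The definition is wrong as written. Literally it yields at most 20 CMT patients and 0 controls, which is incompatible with the planned tests. On a softer reading, never-treated patients leave the CMT arm only, and patients without a 6-MWT leave from either arm. On every reading membership depends on post-randomisation events, so the ITT label is not earned. These conclusions need no assumption.

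The size of any bias cannot be derived from the document. The 0.03 to 0.10 SD is an illustration resting on an assumed 1 to 2 non-starters in 20 and an assumed correlation of 0.3 to 0.5. It is small beside a standard error of about 0.32 SD. The case for correction therefore rests on a main analysis set that cannot be applied as stated, not on a demonstrated large bias. The per-protocol definition shares the gap for controls and needs its threshold reworded.

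**What to change.** In section 2.11:

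1. Define ITT as all randomised patients, analysed in the arm assigned, whether or not they received CMT or completed the 6-MWT. With full recruitment this is 20 against 20.
2. If a treated-and-tested subset is kept, call it modified ITT, make it secondary, and say which 6-MWT (baseline or later) counts as performed.
3. Reword the per-protocol threshold for the CMT arm as at least 80% of sessions (7 of 8), if that is what is meant, and state a rule for controls, for example relevant tests performed and no CMT received.

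This is a change of wording, to be made before the allocation is unblinded for analysis; it needs no further patients. How missing 6-MWT values are handled is a separate question: the article specifies last observation carried forward, and this change of set neither endorses nor replaces it.

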### Safety

2.6

Adverse events (AEs) refer to undesirable, unintended signs, symptoms, or diseases that occur during clinical trials and do not necessarily have causal relationships with the treatments used in the trial. The presence of AEs should be checked at every visit. The severity of AEs is measured using the Common Terminology Criteria for Adverse Events (CTCAE); Grade 1 (Mild): The normal daily activities (functions) are not prevented with only minimal discomfort and the subject can tolerate the symptoms; Grade 2 (Moderate): the normal daily activities (functions) of the subject are significantly inhibited; Grade 3 (Severe or medically significant): The normal daily activities (functions) of the subject are completely inhibited; Grade 4 (life-threatening consequences); Grade 5 (death related to AE). A serious adverse event (SAE) refers to one of the following AEs occurring in a clinical study participant during a clinical trial:

1.death or danger to life;2.hospitalization or extension of hospital stay due to an AE;3.permanent or significant failure or degradation of function;4.development of fetal malformations or abnormalities; and5.other medically important situations.

In the case of SAEs, investigators should report to the sponsor very quickly (usually within 24 hours).

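### The ITT and PP sets are prescribed for all analyses with no exemption for safety, and neither definition suits adverse-event tables

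*Protocol article*

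**What the plan says.** All references are to the protocol article.

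- **Scope of the sets (2.11 Statistical methods):** "For all analyses, the ITT is the main analysis, while the PP is carried out simultaneously, and their results are presented together". No exception is made for safety.
- **ITT set (2.11):** "The subjects who underwent CMT at least once and performed the 6-MWT as the primary outcome". The visit at which the test must be done is not given.
- **PP set (2.11):** "The subjects who received the CMT intervention up to 80% or higher and performed the relevant tests".
- **Missing values (2.11):** last observation carried forward.
- **Aim (2.1 Objective and design):** "The primary purpose of this study is to verify the effectiveness and safety of CMT in combination with Western medicine therapy for COPD".
- **AE collection (2.6 Safety):** "The presence of AEs should be checked at every visit". Collection does not depend on a walk test, and the section names no analysis set.
- **Arms (abstract, Methods):** "an experimental group (n = 20) and a control group (n = 20) at a 1:1 ratio". CMT is given weekly for 8 weeks in the experimental arm, and controls have standard drug therapy alone.

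**The concern.** AEs should be counted in everyone exposed, whether or not an efficacy test was completed. Section 2.11 sends every analysis to sets that require CMT exposure and completed testing. The patients such sets are most likely to lose are those who tolerated treatment worst.

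The article describes itself as the first attempt in South Korea to verify the effectiveness and safety of CMT for COPD, and a full-scale multicentre trial is planned on its results. With 20 patients per arm, one or two patients missing from a table can change how safe the treatment looks. A table without a control denominator would also give no comparison against standard therapy alone.

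**Working it through.** **1. The plan's own figure.** Section 2.7 Sample size says: "the minimum range for efficacy evaluation is set as 16, considering a 20% dropout rate, a total of 40 subjects will be recruited". Reading 16 as per group, 16 / (1 − 0.20) = 20 per arm, and 2 × 20 = 40. The stated total is reproduced, and this point does not affect it.

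**2. Control patients.** ITT membership needs at least one CMT session. Controls have none, so the number of controls who qualify is 0 of 20. The PP definition, which needs 80% of CMT, gives the same result. This does not depend on which 6-MWT counts.

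**3. PP threshold.** There are 8 weekly sessions, and 0.80 × 8 = 6.4, so at least 7 are needed (6/8 = 75% fails, 7/8 = 87.5% passes). A CMT patient who stops for harm after 6 sessions or fewer is outside the PP set. This too holds whichever 6-MWT counts.

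**4. ITT set, CMT arm.** The result depends on what performing the 6-MWT means.

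- *Baseline test qualifies.* An early stopper with a baseline test and one session stays in the set. The loss is 0.
- *A post-baseline test is required.* An early stopper who does not return for it is excluded.

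For the second case, let *w* be the CMT patients who stop for harm before any post-baseline 6-MWT, and *h* the CMT patients with an AE who do perform the test. Then:

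- all-treated proportion = (*w* + *h*) / 20
- proportion in the 6-MWT set = *h* / (20 − *w*)

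The article gives no AE rates, so *w* and *h* are assumed. The upper end, *w* = 4, is the full dropout allowance (0.20 × 20 = 4), used only as a ceiling.

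| *w* | *h* | All treated | 6-MWT set | Gap (points) |
|---|---|---|---|---|
| 1 | 0 | 1/20 = 5.0% | 0/19 = 0% | 5.0 |
| 2 | 0 | 2/20 = 10.0% | 0/18 = 0% | 10.0 |
| 4 | 0 | 4/20 = 20.0% | 0/16 = 0% | 20.0 |
| 1 | 2 | 3/20 = 15.0% | 2/19 = 10.5% | 4.5 |
| 4 | 2 | 6/20 = 30.0% | 2/16 = 12.5% | 17.5 |
| 1 | 4 | 5/20 = 25.0% | 4/19 = 21.1% | 3.9 |
| 4 | 4 | 8/20 = 40.0% | 4/16 = 25.0% | 15.0 |

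Over these assumed counts the CMT AE proportion is understated by about 4 to 20 percentage points, against 0 if a baseline test qualifies.

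**The case against.** The strongest reply is that the sentence was never meant for safety. The methods listed in 2.11 (means and standard deviations, *t* test, Mann–Whitney, ANCOVA, LOCF) are for continuous outcomes, and no AE analysis is described there. Safety has its own section, which names no set. A separate safety set is commonly left to a full protocol or SAP, neither of which is shown.

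Much of this stands. A reader might infer that AE tables will certainly use the ITT set, but no sentence says so. Nor is the mere absence of a safety set a fault in a condensed article. What remains is the rule that is stated: it covers all analyses, and an unseen document with a separate safety set would contradict it.

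A reader might also infer that patients harmed early are bound to vanish from the main set and that the AE rate therefore is biased down. The article does not support that. It names no visit for the qualifying test, the schedule in Table 1 is not available to this review, and under LOCF a baseline value could be carried forward. The wording about the test as the primary outcome leans towards a follow-up measurement but does not settle it.

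Three further limits are fair. The 20% is an all-cause recruitment allowance, not a forecast of stops for harm. The small arms limit what a zero count can rule out in any case, which is a separate matter. And no AE data go uncollected, since checks take place at every visit; only the tabulated population is in question.

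**Conclusion.** The point holds as a moderate one, not as something that must be fixed before the trial can stand. Section 2.11 fixes the analysis sets for everything without exempting a co-primary aim, and both definitions are unsuitable for AEs.

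Two consequences need only the literal wording: no control denominator, and removal from the PP set of CMT patients who stop for harm with fewer than 7 of 8 sessions. The first is probably a drafting fault rather than an intention, since a two-arm comparison is plainly planned.

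The third, loss from the main set, is conditional on a post-baseline 6-MWT being required. Its size, about 4 to 20 percentage points, rests on assumed counts of 1 to 4 early stops for harm and 0 to 4 other patients with AEs; it is zero if the baseline test qualifies.

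**What to change.** In 2.11, limit the ITT/PP sentence to efficacy analyses and add a statement along these lines:

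*Adverse events are analysed in all randomised patients of both arms, grouped by treatment actually received: CMT plus standard therapy if at least one CMT session was given, otherwise standard therapy only. Any patient randomised to CMT who had no session is listed separately. Inclusion does not depend on 6-MWT completion or attendance. No per-protocol analysis of adverse events is done.*

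The explicit handling of CMT-randomised patients with no session is needed; otherwise it is unclear whether they are excluded or counted with controls.

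The cost is a short text change. It needs no new data, visits or patients, because AEs are already checked at every visit. The article reports recruitment as ongoing, so at that stage the change could be made before analysis.

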#### Primary outcome

2.5.1

Primary outcome is the 6-minute walk test (6-MWT). The 6-MWT is a relatively simple and economic test that measures the distance the patient can walk on a flat, hard surface for 6 minutes. The test is commonly used to assess motor function in COPD patients,^[19]^ and it has been regarded as a crucial indicator of exercise tolerance in COPD patients across numerous studies.^[20–23]^

The clinical trial process in presented in Table 1.

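### No single analysis of the 6-MWT is named as primary: a data-chosen t test or Mann–Whitney stands beside an age ANCOVA, and baseline is adjusted for only if it differs significantly

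*Protocol article*

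**What the plan says.** All of this is in the protocol article. The primary outcome is a continuous walking distance: "Primary outcome is the 6-minute walk test (6-MWT"). Statistical methods (2.11) sets one significance level, 0.05, and lists these comparisons for continuous variables:

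1. An unadjusted test that depends on the data: "If the normality assumption is satisfied, an independent *t* test will be carried out; otherwise, the Mann–Whitney *U* test will be carried out".
2. An age-adjusted model with no condition attached: "To adjust for the influence of age, ANCOVA with age as a covariate will be carried out".
3. A further model with a condition: "If a significant intergroup difference is found related to the baseline values, ANCOVA with age and baseline as covariates will be carried out".

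The section ranks the analysis sets, with ITT as the main one and PP reported alongside ("their results are presented together"). It does not rank the tests. It does not say how normality is judged, or whether the endpoint is the follow-up distance or the change from baseline. It does say that continuous results are shown as means and standard deviations.

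Objective and design (2.1) calls the study exploratory, but also gives its primary purpose as verifying effectiveness and safety, and says the results will set the sample size of the later large trial.

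**The concern.** Each analysis set can produce two p-values for the 6-MWT, and sometimes three, with nothing to say which one counts. Three consequences follow.

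- **The question can change with the data.** The t test and a linear ANCOVA both estimate the difference in mean distance. Mann–Whitney compares ranks. If normality is judged to fail, the unadjusted result becomes a rank comparison while the ANCOVA still assumes a linear model for the mean of the same variable.
- **The 0.05 level is not tied to one result.** Anyone free to quote whichever p-value is smallest exceeds it.
- **Baseline is used only by exception.** Baseline 6-MWT is likely to be the strongest predictor of follow-up 6-MWT, yet it enters the model only after a significant baseline test. In a randomised trial that happens by chance about 5% of the time.

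At stake is which estimate, with what precision, is reported as the trial's result and carried into the design of the next trial.

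**Working it through.** **Inputs from the protocol article.** Significance level 0.05 (Statistical methods; two-sided assumed). Arms: "randomly divided into an experimental group (n = 20) and a control group (n = 20) at a 1:1 ratio" (Abstract). Evaluable number per arm: "is set as 16, considering a 20% dropout rate, a total of 40 subjects will be recruited" (Sample size).

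**The plan's own figure.** 16 / (1 − 0.20) = 20 per arm, and 2 × 20 = 40. This reproduces the stated total. The false-positive rate is therefore checked at 16 and 20 per arm.

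**Assumptions not in the documents.** Normal or log-normal distances; baseline/follow-up correlation r of 0.5 or 0.8; age/baseline correlation −0.3; normality judged by Shapiro–Wilk in each arm at 0.05; endpoint taken as follow-up value or as change; baseline compared by t test at 0.05; PP a random 80% of patients. There were 3,000 to 6,000 null trials per setting, so the standard error of a rate near 6% is √(0.06 × 0.94 / 6,000) = 0.3 to √(0.06 × 0.94 / 3,000) = 0.4 percentage points.

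**False-positive rates with the rules applied as written** (t test or Mann–Whitney, never both; age-and-baseline ANCOVA counted only when triggered):

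| Setting | Gate-chosen t/Mann–Whitney alone | Any ITT p-value | One ANCOVA, age + baseline always |
|---|---|---|---|
| 16 per arm, normal | 4.5% to 5.0% | 5.7% to 6.0% | 5.0% |
| 16 per arm, log-normal (r = 0.5) | 4.5% to 4.8% | 6.4% to 6.7% | 4.5% |
| 20 per arm, normal | 4.9% to 5.7% | 5.9% to 6.6% | 5.0% |
| 20 per arm, log-normal | 4.6% to 5.0% | 6.4% to 6.8% | 3.6% |

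Further normal-data runs with r = 0.7 and 0.9 gave 5.3% to 5.5% for the gate alone and 6.5% to 6.9% for any ITT p-value. The highest any-ITT value in any run was 7.6%.

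**How often the gate switches by chance.** With truly normal data, both arms pass with probability 0.95 × 0.95 = 0.90. The simulation at 20 per arm gave 0.897 to 0.904. About 10% of such trials would move to Mann–Whitney for no reason.

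**Precision lost by leaving baseline out.** Take unit variances and follow-up as the endpoint.

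- Residual variance given age only: 1 − (0.3r)².
- Residual variance given age and baseline: 1 − r².
- Ratio of standard errors, before the small cost of one extra covariate: √[(1 − r²) / (1 − 0.09r²)].

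| r | Ratio | Reduction | Reduction in simulation |
|---|---|---|---|
| 0.5 | √(0.75 / 0.9775) = 0.876 | 12% | about 11% |
| 0.7 | √(0.51 / 0.9559) = 0.730 | 27% | about 25% |
| 0.9 | √(0.19 / 0.9271) = 0.453 | 55% | about 54% |

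If the endpoint is the change, the age-only residual variance is 0.91(1 − r)² + 1 − r². The reductions before the covariate cost are then:

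- r = 0.5: 1 − √(0.75 / 0.9775) = 12%.
- r = 0.7: 1 − √(0.51 / 0.5919) = 7%.
- r = 0.9: 1 − √(0.19 / 0.1991) = 2%.

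The large gains therefore belong to a follow-up-value analysis.

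**The case against.** The strongest reply is that this is a small exploratory pilot with no power-based sample size, described in a condensed article, and that an analysis plan not shown could rank the tests. That limits the weight of the point but does not remove it. The article does more than stay silent: it fixes a data-driven choice of test and a conditional baseline adjustment.

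Several stronger readings are tempting, and the documents do not support them.

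- **That the normality gate inflates the error rate.** The gate-chosen test alone stays at about 5% to 6%.
- **That the false-positive rate is about 9.5% to 11%.** That range needs the t test and Mann–Whitney both to count, with the age-and-baseline ANCOVA run in every trial. The plan makes the first two mutually exclusive and the last conditional.
- **That PP adds an unranked set of results.** Letting PP results count too gave 8.2% to 9.6% at 20 per arm, but the plan names ITT as main, so this applies only if that ranking is ignored.
- **That a switch to Mann–Whitney leaves no difference in metres, no SD and no adjustment.** Means and SDs are presented in any case, and the age ANCOVA is still run. What is lost is an unadjusted inference that matches those means.
- **That all the analyses have different estimands.** Only Mann–Whitney differs.
- **That the gate is a formal test applied to raw values.** The text does not say so; Shapiro–Wilk is an assumption of the check above.

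**Conclusion.** The point holds as a moderate weakness that should be corrected. No analysis of the 6-MWT is named as deciding, and the unadjusted and adjusted results can address different questions.

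The excess over 5% is about 1 to 2.5 percentage points. It arises only from freedom to choose among unranked ITT results, and it depends on the assumed distributions and correlations.

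The more important cost is an unclear primary estimate that is usually not adjusted for baseline. How much precision is lost depends on two things the article does not give. One is the baseline/follow-up correlation. The other is whether follow-up or change is analysed: the 11% to 54% range applies to the follow-up value, and with change scores the gain fades as the correlation rises.

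**What to change.** In Statistical methods (2.11), name one primary analysis: the between-arm mean difference in 6-MWT distance with 95% CI, from an ANCOVA that always includes baseline 6-MWT and age, in the main analysis set. With baseline always in the model, follow-up and change give the same treatment estimate, so that ambiguity goes too.

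Remove the normality gate for the primary outcome and the baseline-significance condition. If residuals are clearly skewed, keep the same model and take a bootstrap or permutation interval. Label the unadjusted t test, Mann–Whitney and PP results as supportive.

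The cost is wording only: baseline 6-MWT is already collected, and no patients or visits are added. Trial status (3.1) reports recruitment as ongoing, so from the article's standpoint the change can precede analysis. What is given up is the freedom to choose the test after seeing the data.
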